**Methods:**

This is a three-arm parallel-design cluster-randomized controlled trial. This trial will allocate 12 local secondary schools (clusters) in Hong Kong to three test or comparison groups with a ratio 1:1:1. The enrolled Form II to IV students (ages 12 to 15) will be eligible for participation. The intervention to three study groups will be (i) Health Belief Model (HBM)-based mobile messaging to the adolescents and their parents, which will consist of several blocks of HBM-based messages and reinforcement during 24 weeks; (ii) same HBM-based messaging to adolescents only; and (iii) delivering e-version of oral health education pamphlets to adolescents. The primary outcome will be caries increment 2 years post-intervention. Changes in oral health self-efficacy and behaviors, oral hygiene, and gingival status will be the secondary outcomes.

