### Intervention description {11a}

#### Group (i) family- and HBM-based behavioral intervention via mobile messaging

The mobile messages based on the HBM model will be sent to the students and their parents in two stages over 24 weeks.

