## Outcomes {12}

The primary outcome will be dental caries increment (by tooth level). The students will be examined at the schools at baseline, 1-year, and 2-year follow-up. Dental caries assessment will base on the ICDAS criteria (International Caries Detection and Assessment System), which will be used to assess both non-cavitated (codes 1 and 2) and cavitated caries lesions (codes 3–6) [16]. The examiners will examine occlusal, mesial, distal, buccal, and lingual surfaces of each tooth.

The secondary outcomes will be:i)Gingival status measured by the percentage of sites with gingival bleeding (BOP%), as recommended by the WHO for conducting oral health surveys [1];ii)Oral hygiene status using the Visible Plaque Index (VPI). The percentage of plaque on the buccal and lingual surfaces of all indicated teeth will be recorded [1];iii)Average frequency of toothbrushing per day (2 times as preferred);iv)Average frequency of intake of sugary snacks/drinks per day (2 times or less frequent as preferred);v)Average amounts of free-sugar intake per day (<25 g as preferred); andvi)Oral health self-efficacy on behaviors (questionnaire score rated on a 4-point Likert scale, e.g., 1 = not confident at all to 4 = very confident)

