## Statistical methods

### Statistical methods for primary and secondary outcomes {20a}

The effectiveness of HBM-based intervention will be evaluated by comparing the differences in the outcome variables among the three groups. For the primary outcome, linear mixed models will be constructed to compare the dental caries increment and other continuous outcome variables such as BOP% and VPI over time. Socio-demographic variables (gender and parental education level) will be controlled for. Three-level random intercept models will be considered for evaluating the clustering effect and longitudinal data: time as level 1, students as level 2, and schools as level 3 so that the interaction between times and intervention groups would be tested. Multi-level logistic regression adjusting for the effects of possible confounding factors for the clustered data [21] will be performed to test the differences in the prevalence of dental caries, and proportions of other categorical outcome variables such as frequency of toothbrushing and sugar intake among the three groups. The level of statistical significance for all tests will be set at 0.05. All the analyses will be performed using the SPSS software package.

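### The one specific test named for the caries increment, time by group, is not the 24-month comparison on which the trial is defined and sized, unless caries level is the response

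*Protocol article*

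**What the plan says.** The abstract fixes the quantity and the time point: "The primary outcome will be caries increment 2 years post-intervention". The outcomes section {12} also makes the increment primary, and gives the visits: "The students will be examined at the schools at baseline, 1-year, and 2-year follow-up". The sample size section {14} uses the same quantity, a one-way ANOVA on the 24-month change in DMFT, with means 0.12 and 0.34 and SD about 0.50.

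The statistical methods section {20a} opens by saying that effectiveness "will be evaluated by comparing the differences in the outcome variables among the three groups". It then says that "linear mixed models will be constructed to compare the dental caries increment and other continuous outcome variables such as BOP% and VPI over time". On structure: "Three-level random intercept models will be considered for evaluating the clustering effect and longitudinal data", with time as level 1, students as level 2 and schools as level 3, "so that the interaction between times and intervention groups would be tested". No group contrast at 2 years is named.

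In group (i) the messages "will be sent to the students and their parents in two stages over 24 weeks", and group (ii) has the same 24 weeks, so messaging ends before the 1-year examination.

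**The concern.** An increment is already a change from baseline. If it is the response in a model over time, only two values per student exist, at years 1 and 2. A time-by-group term then takes a second difference: it asks whether the gap between arms widens or narrows between the two follow-ups, not whether the arms differ at 2 years. BOP% and VPI are levels measured at baseline as well, so for them the interaction is a comparison of changes and makes sense. Section {20a} applies one recipe to both kinds of variable.

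At stake is the primary conclusion. The trial could achieve the planned 0.22 difference and report a null on its named test. Conversely, arms with equal 2-year increments but different timing could give a significant interaction. Because messaging stops at week 24, a benefit that is largely present by year 1 is possible.

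**Working it through.** **Inputs from the protocol.** 24-month means 0.12 and 0.34, SD about 0.50, effect size 0.21, alpha 5%, power 80%, ICC 0.03, 75 students per school, 4 schools per arm, 10% dropout (section {14}); visits at 0, 1 and 2 years (section {12}).

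**Assumptions, not in the protocol.** One arm is 0.22 below the other two at 2 years. The share of that benefit present by year 1 is 50%, 75% or 100%. For the noncentral-F figures, the year-1 increment has SD 0.50 × √0.5 = 0.354 and its correlation ρ with the 2-year increment runs from 0.5 to 0.85.

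**The plan's own figures.** A three-group ANOVA with f = 0.21 and 74 per group (222 in all) has power 0.801, so 74 reproduces. Design effect: 1 + (75 − 1) × 0.03 = 3.22. Then 74 × 3.22 = 238.3, and 238.3 / 0.9 gives 265 per group. The planned 300 exceeds this and equals 4 × 75. The sizing therefore rests on the 24-month group comparison.

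**Power of that comparison.** Completers: 900 × 0.9 = 810, or 67.5 per school. Design effect 1 + 66.5 × 0.03 = 2.995; effective N = 810 / 2.995 = 270. With one arm lower by d, f = d × (√2/3) / SD. For d = 0.22 and SD 0.50, f = 0.207 and power is 0.87 (noncentral F). A simulation of 12 school means (67 completers each, 20,000 runs, F test on 2 and 9 df, independent yearly increments of equal variance) gives about 0.73. Neither depends on when the benefit arises.

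**Reading A: cumulative increments Y1 and Y2 as response.** Interaction = (difference in Y2) − (difference in Y1) = difference in caries gained in year 2. The relevant SD is √(0.125 + 0.25 − 2ρ × 0.354 × 0.50), which is 0.445 at ρ = 0.5 and 0.273 at ρ = 0.85.

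| Benefit present by year 1 | Target of interaction | Power, ρ = 0.5 to 0.85 | 12-school simulation |
|---|---|---|---|
| 50% (linear accrual) | 0.22 − 0.11 = 0.11 | 0.38 to 0.80 | 0.43 |
| 75% | 0.22 − 0.165 = 0.055 | 0.12 to 0.27 | 0.14 |
| 100% | 0.22 − 0.22 = 0 | 0.05 | 0.05 |

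The last row holds for any SD or correlation, because the target is exactly zero.

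**Reading B: separate yearly increments as response.** Interaction = (difference in year-2 gain) − (difference in year-1 gain). If benefit is equal in both years, 0.11 − 0.11 = 0 and the simulated rejection rate is 0.05. If it is all in year 1, power is about 0.72. This too is not a test of the 2-year increment.

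**Reading C: DMFT level at 0, 1 and 2 years as response.** With linear time and complete data, the slope weights are (−0.5, 0, 0.5). Twice the slope difference is the difference in level at year 2 minus that at baseline, which is 0.22 in size for any timing. With categorical time, the interaction has (3 − 1) × (3 − 1) = 4 df. On the same effective sample (about 90 per arm), with year-1 SD 0.35 to 0.50 and correlation 0.5 to 0.85, its power is 0.82 to 0.99 if all benefit is present by year 1 and 0.79 to 0.93 under linear accrual. It is not blind to early benefit, but it is not the single comparison used for sizing.

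**The case against.** The strongest reply is that the interaction is not clearly the primary test. Section {20a} begins with differences among the three groups, the three-level models are only to be considered, and one sentence serves caries, BOP% and VPI together. The abstract already fixes the 2-year time point. A trialist could also treat the increment as the time effect in a model of caries level, as in reading C, and then the defect disappears. The coding of time and the choice of contrast are often left to an SAP, and this is a condensed article.

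Much of this stands. A 2-year group comparison is not excluded, and the effect of the wording depends on the response variable. A reader might infer that the planned analysis is bound to miss an early benefit, or that it is wrong however caries is modelled; the documents support neither. Nor does half the target mean half the power, since the year-2 gain may vary less than the 2-year increment. The protocol gives no time course for the effect, and its stated hope of lasting habits would favour continued divergence after messaging ends.

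What does not stand is that this is only missing detail. The section states a response, the increment, and a specific test, the interaction. Taken together as written, they do not answer the primary question. The opening sentence names neither a time point nor a contrast, so it does not settle the matter.

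**Conclusion.** The point holds conditionally. On the literal wording (reading A), the named test targets the arm difference in year-2 caries only: 0.11 of the planned 0.22 under linear accrual, and 0 with power equal to alpha if all benefit is present by year 1. Under reading B it is blind to a benefit equal in both years. Under reading C there is no blind spot, and with linear time the interaction is the 24-month difference itself.

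The zero targets follow from algebra alone. The intermediate power figures, and the 0.73 to 0.87 for the direct comparison, rest on the assumed pattern of arm means and, for the interaction, on the assumed timing, year-1 SD and correlation. Because the wording bears on the primary conclusion and leaves room to choose the test after the data are seen, it should be settled before analysis.

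**What to change.** State in section {20a} that the primary test is the between-arm difference in 24-month caries increment, with school as a random effect. Equivalently, state that DMFT level at 0, 1 and 2 years is modelled and that the baseline-to-year-2 group contrast is primary. Make any overall time-by-group test on the increment secondary. The interaction may stay for BOP% and VPI. Extra covariates, or a different test for those two outcomes, are separate preferences and not needed to resolve this point.

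The cost is a few sentences in the analysis section. No visit, measurement or change in sample size is needed, and the analysis then matches the quantity on which the 74 per group was calculated.

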### Trial design {8}

This study is a three-arm parallel design, superiority, cluster-randomized controlled trial comparing three interventions. Interventions will be applied at the cluster (school) level. Either active or comparator intervention is administered to the school by randomization to prevent contamination. The allocation ratio is 1:1:1.

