## Sample size {14}

The sample size has been calculated using G*Power software. Our previous study showed that motivational interviewing was more effective than prevailing OHE in preventing dental caries among adolescents [17]. In this proposed study, the sample size is calculated based on mean and standard deviations of the primary outcome measure — the number of new carious teeth (∆DMFT). From the pre-existing study, an effect size of 0.21 was obtained for tooth status over 24-month evaluation (∆DMFT: test group=0.12 vs. control group=0.34; SD ~ 0.50) [18], which could be considered a moderate size convention for 1-way ANOVA and clinically significant for the primary outcome [19]. Based on a significance level of 5% and a targeted statistical power of 80%, 74 participants in each group will be required. Considering a typical value of ICC = 0.03 in a cluster randomized clinical trial setting [20] and if 75 children are to be recruited from each school, the design effect will be 3.22 [21]. Assuming a similar dropout rate as our previous study in secondary school at the 2-year follow-up (dropout rate: 10%) [17], the sample size will be increased to 300 in each group, thus 900 altogether. Then 4 schools in each group, a total of 12 schools will be recruited.

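### Categorical outcomes are tested at 0.05 across only 12 schools with no small-sample inference specified; uncorrected large-sample tests would reject a true null about 7% to 15% of the time

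*Protocol article*

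**What the plan says.** Section {20a} of the protocol article assigns "Multi-level logistic regression adjusting for the effects of possible confounding factors for the clustered data" to caries prevalence and to other categorical variables, with toothbrushing and sugar frequency as examples, compared across the three arms. It then says: "The level of statistical significance for all tests will be set at 0.05". On software it says: "All the analyses will be performed using the SPSS software package". It names no estimator, reference distribution or degrees-of-freedom rule for these models.

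The number of clusters comes from Sample size {14}: "Then 4 schools in each group, a total of 12 schools will be recruited". Trial design {8} applies the interventions at school level, and Study setting {9} allocates the schools within three geographical regions (3, 6 and 3 schools). Clustering enters the sample size through one assumption, "Considering a typical value of ICC = 0.03 in a cluster randomized clinical trial setting", and its consequence, "if 75 children are to be recruited from each school, the design effect will be 3.22".

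**The concern.** With whole schools allocated, the arm effect on a binary outcome is a contrast between school results. Its precision rests on a between-school variance estimated from 12 schools. Two things go wrong when large-sample methods are used with so few. A z or chi-square reference treats that variance as known, and maximum likelihood also tends to estimate it too low. Both make standard errors too small relative to the reference distribution, so p-values are too small and intervals too narrow.

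The design effect of 3.22 does not cover this. It enlarges the sample for the correlation within schools, but says nothing about how poorly 12 schools estimate the variance between them.

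At stake are the comparisons that carry the behavioural part of the objective in {7}. Favourable behavioural results are among those {31a} would bring to the government health department. A correction confined to the linear mixed model for the primary outcome would not reach them.

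**Working it through.** **1. The plan's own figures.** Means of 0.12, 0.34 and 0.34 with SD 0.50 give f = 0.207, close to the stated 0.21. A one-way ANOVA with three groups, f = 0.21 and 74 per group has power 0.801, so 74 reproduces. The design effect is 1 + (75 - 1) × 0.03 = 3.22. Then 74 × 3.22 = 238.3; 238.3 / 0.9 = 264.8, or 265; 265 / 75 = 3.5, rounded up to 4 schools, which is 300 per group. The sample-size arithmetic is not in question.

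**2. Degrees of freedom.** There are 12 schools and 3 arm means, leaving 12 - 3 = 9. Two further parameters for the three regions leave 7.

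**3. Closed-form guide at nominal 5%.**
- Reference distribution alone: P(|t9| > 1.96) = 8.2% for a pairwise contrast. For three groups, P(F(2,9) > 5.99/2) = 10.1%.
- If maximum likelihood also shrinks the variance by 9/12, the cut-offs become 1.96 × √0.75 = 1.70 and 2.996 × 0.75 = 2.25, and the tail areas rise to 12.4% and 16.2%.

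**4. Simulation under no effect.** Inputs: 12 schools, 4 per arm; 75 students per school, or 68 after 10% dropout; ICC 0.03, set either on the probability scale or on the latent logistic scale. The event rates of 23% to 50% include the 23%, 32% and 36% that the Discussion reports from the Hong Kong survey. There were 4,000 to 8,000 simulated trials per setting, with a Monte Carlo standard error of about 0.3 to 0.6 points.

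| Estimator and test (nominal 5%) | Rejection of a true null |
|---|---|
| ML, pairwise Wald z, 12-school model | 10.4% to 12.0% |
| ML, pairwise Wald z, two-arm fit to 8 schools | 10% to 13% |
| ML, three-group Wald chi-square | 13.7% to 15.4% |
| ML, three-group likelihood ratio | 9.3% to 10.3% |
| Restricted pseudo-likelihood, pairwise z | 6.7% to 8.9% |
| Restricted pseudo-likelihood, three-group chi-square | 8.7% to 9.8% |
| ML with t(9) or F(2,9) | about 6% to 8% |
| Restricted pseudo-likelihood with t(9) or F(2,9) | 3.9% to 5.1% |
| School-level ANOVA of proportions, F(2,9) (run at 23% to 36%) | 4.3% to 5.5% |

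The lowest and highest uncorrected results are 6.7 / 5 = 1.3 and 15.4 / 5 = 3.1 times the nominal level.

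**5. Sensitivity.** At a 10% event rate with the ICC on the latent scale, the uncorrected tests reject 6.5% to 10.6%. At a 10% rate, restricted pseudo-likelihood on 9 df is conservative, at 2.3% to 4.5%. A smaller run (1,500 trials per setting, 67 students per school, rate 68%) gave pairwise ML Wald z rejection of 8.3% at ICC 0.01 and 11.5% at ICC 0.05.

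**The case against.** The strongest reply is that the article does not commit to large-sample inference. Section {20a} names a model, a level and a package. Multilevel logistic regression with a proper degrees-of-freedom rule fits that text equally well, and an analysis plan not shown here could supply the rule. This stands, and it makes the point conditional. A reader might infer that the planned method, as written, has an error rate of 11% to 13%, or more than twice the nominal level. The documents do not support that. Such figures belong to a pairwise Wald z test after full maximum likelihood, which {20a} does not specify. Several other large-sample versions stay below 10%, and the three-group Wald test goes above 13%.

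The inputs are also partly borrowed. The ICC of 0.03 was adopted to size a continuous outcome, and no ICC is given for any binary one. The survey rates are not the trial's own: the 23% refers to 12-year-olds, whereas the trial follows 12- to 15-year-olds for two years and also scores non-cavitated lesions. The survey's snacking category also differs from the cut-point in Outcomes {12}. The simulation used one time point, equal school sizes, no covariates and no region. All of this stands as a limit on precision, and is why a range is given.

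The scope is modest too. Outcomes {12} does not list caries prevalence, and it lists toothbrushing and snack frequency as daily averages, so how far the logistic models will be used is not clear.

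The reply does not remove the problem. The article sets 0.05 for all tests and 4 schools per arm. At rates of 23% to 50% and ICC 0.03, every uncorrected large-sample version checked missed that level.

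**Conclusion.** The point holds in conditional form. Unless small-sample inference at school level is used, tests of arm effects on categorical outcomes run at about 7% to 15% instead of 5%, according to estimator and test. This assumes that ICC 0.03 carries over to the binary outcomes and that event rates lie between 23% and 50%. At a 10% rate or a smaller ICC the excess can be smaller, but it was still present in the settings run.

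The calculations concern the logistic models only. A reader might extend the figures to the primary caries increment. That outcome is assigned a linear mixed model, which was not simulated here, so these percentages say nothing about it. Because secondary and supporting analyses are affected, this should be corrected before analysis but does not undermine the design.

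**What to change.** State in {20a} that arm effects on all categorical outcomes are tested with school-level small-sample inference, by one named method:

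- a school-level analysis of covariate-adjusted log-odds or proportions, using t for pairwise contrasts and F for the three-group test on 9 degrees of freedom (7 if region is included); or
- the multilevel logistic model fitted by restricted pseudo-likelihood, with t or F on the same degrees of freedom.

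Add that large-sample Wald p-values will not be reported for arm effects, and that confidence intervals use the same reference distribution. Maximum likelihood with t on 9 degrees of freedom is not enough by itself, since it still rejects about 6% to 8%.

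The change is a few sentences of wording and needs no extra schools, students or data. Its price is wider intervals and fewer nominally significant secondary results, with some conservatism from restricted pseudo-likelihood for outcomes near a 10% rate.

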### Objectives {7}

The objective of this study is to investigate the effectiveness of the family- and HBM-based mobile-health behavioral intervention in enhancing adolescents’ good oral health behaviors (mainly oral hygiene practice and free sugar intake control) and preventing common oral diseases (dental caries and periodontal diseases).

The research hypothesis is the proposed family- and HBM-based mobile-health behavioral intervention is more effective than intervention on the adolescents alone or prevailing OHE in improving the adolescents’ behaviors and oral health.

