## Discussion

The population-based oral health survey in Hong Kong [23] has shown that 23% of 12-year-old children in Hong Kong had caries experience. Although the extent/severity of caries was low (mean DMFT 0.4), most 12-year-old children (86%) had gingivitis, and calculus was prevalent (64%). The lower prevalence of caries among the Hong Kong adolescent population is associated with the School Dental Care Service provided by the Department of Health, which includes a range of preventive and basic dental care for grade 1 to 6 primary school children. However, School Dental Care Service is not available to secondary school students. Additionally, this survey [23] has shown that 32% of the adolescents did not brush their teeth twice per day and that 36% snacked twice per day or more often. We also found that the oral health status worsened from childhood to early adulthood following a cohort of 638 students from 12 to 18 years old in Hong Kong [24]. Hence, there is a strong need to deliver oral health education among this specific age group, highlighting the significance of this proposed project.

For improving oral health in adolescents, this study would be a first step towards the mobile-health-associated Sustainable Development Goals by the WHO [25], as there are no mHealth-driven oral health activities among adolescents in Hong Kong. For there is no governmental oral health service to secondary school students, we hope such a simple intervention using modern-day technology may facilitate positive health behaviors among adolescents, which benefit them for a lifetime.

The innovation of this trial is the combination strategies which is still controversial about the effectiveness of two levels of influence in socio-ecological models (individual and family). Besides, the intervention is theoretically informed, drawing from a behavioral theory from the social-psychological field.

The limitation of this study is the person who can receive the message via smartphone will be recruited, without covering the poor communities with no smartphones. There is a concern about generalizability. Besides, the participants are limited to the cohort of youth in school, therefore the outcomes could not be generalized to the out-of-school adolescents as there could be potential peer effects in our study participants.

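### The supporting binary caries test uses prevalence, which includes pre-trial disease; it is a diluted test of prevention compared with any new carious tooth

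*Protocol article*

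**What the plan says.** The Objectives section aims at "preventing common oral diseases (dental caries and periodontal diseases". The Outcomes section states: "The primary outcome will be dental caries increment (by tooth level". The sample size rests on the mean number of new carious teeth (∆DMFT), with "test group=0.12 vs. control group=0.34; SD ~ 0.50".

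The section on statistical methods for primary and secondary outcomes plans two caries analyses. The first is a linear mixed model on the increment. The second is a multilevel logistic regression, adjusted for confounders that are not itemised, "to test the differences in the prevalence of dental caries, and proportions of other categorical outcome variables such as frequency of toothbrushing and sugar intake", compared among the three groups. It is a significance test like the rest: "The level of statistical significance for all tests will be set at 0.05".

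Caries prevalence appears in neither the primary nor the secondary outcome list. The only baseline figure in the document is in the Discussion: "23% of 12-year-old children in Hong Kong had caries experience".

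**The concern.** If caries is counted as cumulative experience (DMFT), a student who is positive at baseline stays positive in every arm. New caries in that student cannot change the prevalence outcome. The arm difference is therefore carried only by students who were caries-free at baseline, while differences between schools in pre-trial disease add noise, with only 4 schools per arm.

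The practical risk is a non-significant prevalence result beside a significant increment result. That would look like conflicting caries evidence when it comes only from the choice of binary variable.

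**Working it through.** **1. The plan's own figures.** The plan says "an effect size of 0.21 was obtained for tooth status over 24-month evaluation". Taking arm means 0.12, 0.34 and 0.34, the grand mean is 0.267 and the SD of the means is √[(0.147² + 0.073² + 0.073²)/3] = 0.104. Then f = 0.104/0.50 = 0.207, close to 0.21. A noncentral F calculation (3 groups, f = 0.21, alpha 0.05) gives 74 per group with power 0.801, which matches "Based on a significance level of 5% and a targeted statistical power of 80%, 74 participants in each group will be required". The design effect is 1 + (75 − 1) × 0.03 = 3.22. Next, 74 × 3.22 = 238.3 and 238.3/0.9 = 265 per group, taken up to 4 × 75 = 300. The sample size reproduces. No power is stated for the binary test.

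**2. Converting the effect to proportions (assumptions).** If new carious teeth are Poisson, the proportion with any new carious tooth is 1 − exp(−mean):
- test: 1 − exp(−0.12) = 11.3%
- control: 1 − exp(−0.34) = 28.8%

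The implied SDs, √0.12 = 0.35 and √0.34 = 0.58, lie on either side of the plan's 0.50.

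If experience is irreversible and new caries is independent of baseline status, 2-year prevalence is b + (1 − b) × incidence, where b is baseline prevalence. With b = 23%:
- test: 0.23 + 0.77 × 0.113 = 31.7%
- control: 0.23 + 0.77 × 0.288 = 45.2%

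The difference shrinks from 17.5 to 13.5 points, and the binomial variance rises.

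**3. Pairwise approximation.** The effective n per arm is 300 × 0.9/3.22 = 83.9. The calculation is a two-proportion test, two-sided 0.05.

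| Baseline prevalence | Power, any new carious tooth | Power, 2-year prevalence | Loss (points) |
|---|---|---|---|
| 10% | 81% | 62% | 19 |
| 23% | 81% | 43% | 38 |
| 30% | 81% | 36% | 46 |
| 40% | 81% | 27% | 54 |
| 50% | 81% | 21% | 60 |

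Other shapes of new caries:
- Exactly one new tooth per affected student (12% vs 34%): at b = 23%, power falls from 93% to 61%, a loss of 32 points; at b = 10%, from 93% to 80%, a loss of 13.
- Students with baseline caries have 2 to 3 times the rate of new caries: at b = 23% the loss is 46 to 50 points; at b = 50% with 3 times the rate it reaches 69.

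**4. School-level simulation.** Settings: 4 schools per arm, 68 examined per school (75 less 10%), means 0.12/0.34/0.34, ICC 0.03, b = 23%, three-arm ANOVA on school proportions with 9 error degrees of freedom.

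| Outcome | Power |
|---|---|
| Any new carious tooth | 75% |
| 2-year prevalence, baseline ignored | 41% |
| 2-year prevalence, baseline ignored, almost no school clustering of baseline caries | 57% |
| Change in prevalence from baseline | 67% |
| 2-year prevalence among students caries-free at baseline | 70% |

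Using baseline therefore leaves a loss of 75 − 70 = 5 to 75 − 67 = 8 points. With twice the rate of new caries in baseline-positive students, the two baseline-using versions have 67% and 64% against 74%, a loss of 7 to 10. With 0.23 in all arms, rejection is 0.051 for prevalence and 0.061 for any new carious tooth, both near 5%.

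**The case against.** The strongest reply is that the document does not fix how the logistic model uses baseline. The sentence before it describes time/student/school models with a time-by-group interaction, and baseline caries could be among the confounders. Exact covariates for a supporting model are commonly left to an analysis plan, so the missing list is no fault. This stands. It is why the loss of about 35 points applies only to a comparison that ignores baseline, and why 5 to 10 points must be stated beside it. What the reply does not remove is the named endpoint: prevalence is chosen in the text, is not a listed outcome, and has less power than any new carious tooth on each reading examined.

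A reader might infer three stronger points that the documents do not support.
- *The test does not address prevention.* Under randomisation, baseline prevalence is equal in expectation. If experience is irreversible, a systematic 2-year difference must come from new caries. The test is diluted, not aimed at another question.
- *Chance imbalance between schools would produce false effects.* Imbalance costs precision, but rejection under the null stays near 5%.
- *The trial's conclusion on caries is at risk.* The primary outcome, primary model and sample size all use the increment.

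The caries threshold for this test is also not stated. Irreversibility fits DMFT. Whether it fits ICDAS codes 1 and 2, which the Outcomes section also records, is an open assumption, so the rows with higher baseline prevalence are illustrations.

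**Conclusion.** The point holds as a weakness of a supporting analysis. Prevalence mixes old and new disease and is a less precise test of prevention than any new carious tooth.

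At the plan's effect and 23% baseline experience, power is about 40% against about 75% if baseline is ignored. The loss runs from about 20 to 60 points over 10% to 50% baseline prevalence and with little or no school clustering of baseline caries; changing the distribution of new caries as well can move it outside that range, as the working shows. If the model uses baseline status, the loss at 23% is about 5 to 10 points.

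None of these is a figure of the document. They rest on the Poisson conversion, on irreversible caries experience, on a figure for 12-year-olds applied to ages 12 to 15, and on an assumed clustering of baseline caries. The direction is the same throughout; the size is not fixed.

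**What to change.** In the section on statistical methods for primary and secondary outcomes, replace caries prevalence as the tested binary variable with the proportion of students who have at least one new carious tooth (∆DMFT > 0) between baseline and the 2-year examination. Keep the same multilevel logistic model, and report prevalence at each visit descriptively.

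The cost is one sentence. Both examinations are already scheduled, so no new data or participants are needed. The small downside is that each student needs a paired baseline and 2-year examination, which the primary increment already requires.
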